### Sample size estimation

Power analyses were generated using the two-group repeated proportions module in NCSS PASS 14 [40] to compute minimum detectable effect sizes for the primary analysis. Assuming α = 0.05, power = 0.80, rho = 0.43 and a 7-day abstinence base rate of 3.2% and a quit rate of 8.3% in the treatment group from our preliminary data [31], group sample size of 234 (N_total_ = 468) is needed. Assuming a dropout rate of 7%, we need 500 participants.

### Recruitment

A total of 500 participants will be recruited using social media campaign strategies that have been successfully employed in previous online survey and intervention studies [31, 41], augmented by outreach through community partners and youth serving organizations. Advertisements will be targeted based on age and with keywords likely to reach e-cigarette and social media users. Ads will include an image and short text consistent with most social media advertising guidelines. Most ads will mention study incentive. Ad spending and response (clicks on ads and study enrollment numbers) will be monitored with adjustments as needed to maximize efficiency of spending. Ads will include a link to the study’s website www.quitthehitca.com, which has a short description of the study and eligibility questions that address the inclusion criteria and exclusion criteria. If respondents are eligible, then they will be taken to the informed consent page. The participant flow through the RCT is shown in Fig. 1.

**Fig. 1 Fig1:**
[figure not shown]
Participant flow through the randomized clinical trial

### Study procedure

The state of California allows teenagers to seek treatment for substance use without parental consent [42]. Parental consent may pose a risk to teens by revealing their vaping behavior, which may make them reluctant to engage in vaping cessation interventions. Therefore, in this study, both young adult participants and adolescent participants will consent to participate in the research themselves. Participants will complete consent electronically on the study website immediately following completion of eligibility screening. The consent forms will contain a thorough description of the research project, including the procedures involved, the benefits and risks, compensation, the right to non-participation, and the Research Subject’s Bill of Rights. These documents are also available to participants at any time on the study website: www.quitthehitca.com. The amount of text in the standard consent form is burdensome to read on a mobile device, and participants may tend to skip the form. To enhance usability, especially for mobile devices, a shortened version of the consent form and a video version of the consent with key elements have been created for mobile device review and consent. Participants on mobile devices will also have the opportunity to download and save the full consent form for future viewing.

Information about the informed consent process is written in clear, concise English that can be understood at a 6th-grade reading level. Participants will be asked to contact study staff if they do not understand any part of the informed consent information.

Before being able to proceed with the study, participants will indicate on an electronic form that they understand what this study is about, that their participation is voluntary, that they are not required to complete any part of this study, and that there are risks associated with study participation. Incomplete or incorrect answers will result in the potential participant being prompted to review the full consent document before attempting the consent questions again. Potential participants will not be enrolled in the study if they fail to complete the form four times. In both the screening and baseline survey, participants are asked about location questions (zip code in the screening and county in the baseline survey). Our research staff will check the consistency of their answers and contact the participants with inconsistent answers using the contact information they provided to confirm the authenticity of the participants. In addition, participants must follow the study account on Instagram, and study personnel will review the profiles of followers for consistency with age and California location. Irregular or inconsistent answers or participants otherwise having difficulty completing the form will be contacted by trained study personnel who will review the consent material and assist with study enrollment. Study personnel may detect behavior, responses or Instagram accounts that do not appear to be authentic. Fraudulent participants identified through this process will be removed and documented. In the consent form, participants will be asked to remain in the study’s Instagram group throughout the duration of the study (about 7 months) for the intervention and for follow-up contacts. Participants will be paid $10 in the form of an electronic gift card for completing the baseline assessment. Participants will be paid $15–35 for each follow-up assessment for a possible total of $100.

Participants who sign the consent form will be asked to create a login, and then redirected to the baseline assessment. This study will recruit 500 participants in total. Those completing the baseline assessment are randomized using a computer-generated random sequence which automatically assigns participants without revealing allocation to study investigators. Participants are assigned to either the Instagram intervention or the control condition, which is a referral to free support administered by the California quitline via the website kickitca.org. Approximately two weeks after the first participant is enrolled in an intervention group, the group will begin to receive the intervention program. Groups may start slightly sooner or later than 2 weeks based on the pace of recruitment, aiming for a group size between 5 – 15 participants. Depending on the pace of enrollment, multiple groups may run simultaneously.

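### Allocation is tied to completing the baseline survey, and nothing makes it wait for the authenticity and residence checks that depend on that survey

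*Protocol article*

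**What the plan says.** All of the following is in the Protocol article.

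- **Trigger for allocation (Study procedure).** "Those completing the baseline assessment are randomized using a computer-generated random sequence which automatically assigns participants", with the allocation hidden from the investigators. Completing baseline is the only condition named; verification status is not mentioned.
- **Location check (Study procedure).** At two points "participants are asked about location questions (zip code in the screening and county in the baseline survey") are collected. Then "Our research staff will check the consistency of their answers and contact the participants with inconsistent answers".
- **Profile check (Study procedure).** "participants must follow the study account on Instagram, and study personnel will review the profiles of followers for consistency with age and California location". No timing is given.
- **Open-ended detection (Study procedure).** "Study personnel may detect behavior, responses or Instagram accounts that do not appear to be authentic". Those judged fraudulent are taken out and recorded. The text gives no time limit, no blinding to arm and no rule on replacement.
- **Target (Recruitment).** "A total of 500 participants will be recruited using social media campaign strategies". Whether the 500 are verified participants is not said. Sample size estimation derives 500 from 468 with a 7% dropout allowance and nothing else.
- **Analysis set (Data analysis).** The self-report analysis covers participants who are still in the study.
- **Observation by arm (Intervention group, Control group, Discussion).** The Guide watches daily conversation in the Instagram groups, and problem content there can lead to disqualification. Controls are referred to a website.

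**The concern.** The zip-county comparison cannot begin until the county question in the baseline survey is answered. Finishing that survey is also the only stated condition for assignment. The check then takes staff time and sometimes contact with the participant. Without a hold between the two steps, an account that later fails can already have an arm.

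Three consequences follow:

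- **Lost sample.** Removed accounts may occupy places among the 500 that were meant for genuine participants.
- **Removal informed by arm.** The grounds for suspicion include behaviour, and intervention participants can generate group behaviour that controls cannot. The same false account may be easier to find in one arm.
- **Effect on the analysis.** Whoever is removed leaves the self-report set. Whoever is missed stays in it and contributes whatever they report.

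The setting makes this worth closing. Most advertisements mention the incentive, payments can reach a possible total of $100, and the protocol itself expects some fraudulent entrants.

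**Working it through.** **Inputs from Sample size estimation:** alpha 0.05 (two-sided assumed), power 0.80, rho 0.43, abstinence 3.2% against 8.3%, 234 per arm, 7% dropout, 500 in total. Outcome measures gives three follow-ups. **Assumed, because the document gives no figures:** the fraudulent share f, the detection rate in each arm, and what fraudulent accounts report.

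**1. Reproducing the plan's figure.** With p1 = 0.032, p2 = 0.083 and mean 0.0575, the pooled two-proportion formula for one time point is

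n = [1.960 x sqrt(2 x 0.0575 x 0.9425) + 0.8416 x sqrt(0.032 x 0.968 + 0.083 x 0.917)]² / 0.051² = 326 per arm.

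The repeated-measures factor is (1 + (T - 1) x 0.43) / T.

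- T = 2: 0.715 x 326 = 233.1, so 234. This matches the plan.
- T = 3: 0.62 x 326 = 202.1, so 203.

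The stated 234 therefore corresponds to two measures, although three are planned. That errs on the safe side, and power is shown below on both bases.

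**2. Slack in the 500.** 468 / 0.93 = 503.2, so 504; 468 x 1.07 = 500.8, so 501. The 500 is close to both. But 500 x 0.93 = 465, already 3 below 468, so nothing is left for removals.

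**3. Power if a share f is removed and not replaced.** Retained per arm: m = 500 x (1 - f) x 0.93 / 2. Power is computed at m / 0.715 (T = 2) or m / 0.62 (T = 3).

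| f | m per arm | Power, T = 2 | Power, T = 3 |
|---|---|---|---|
| 0% | 232.5 | 79.9% | 85.2% |
| 5% | 220.9 | 77.9% | 83.4% |
| 10% | 209.25 | 75.6% | 81.4% |
| 20% | 186 | 70.6% | 76.7% |

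**4. Bias if some fraudulent accounts stay in and detection differs by arm.** This is a separate scenario from step 3, and the two should not be added together. Take 250 per arm, detection of 90% in the intervention arm and 50% in controls, half of the undetected accounts reporting abstinence, and none passing the cotinine test. Genuine participants are taken to have the planning rates, a true difference of 5.1 points.

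At f = 10% there are 225 genuine per arm, with 2.5 and 12.5 undetected:

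- Self-report: (225 x 0.083 + 1.25) / 227.5 = 8.76% against (225 x 0.032 + 6.25) / 237.5 = 5.66%. The difference is 3.1 points.
- Verified: 18.675 / 227.5 = 8.21% against 7.2 / 237.5 = 3.03%. The difference is 5.2 points.

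Over f = 5% to 20%, the self-reported difference runs from 4.1 down to 0.9 points, and the verified difference stays between 5.1 and 5.3.

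**5. The opposite direction.** Suppose fraudulent accounts are never abstinent, all are found in the intervention arm and half in controls, and f = 20%. A true 8.3% in both arms then shows as 8.3% against 200 x 0.083 / 225 = 7.4%, a spurious 0.9 points in favour of the intervention. At f = 10% it is 8.3% against 7.9%.

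**The case against.** The text describes the checks before it describes randomisation, makes following the study account a requirement, and says staff contact will help with enrolment. A team could well be verifying first. The article also condenses a fuller protocol in which a hold step might appear. This stands as a possible reading. But the enrolment remark concerns irregular answers and difficulty with the form, and the one sentence on allocation conditions it on baseline completion alone.

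A reader might infer three stronger things, and the document supports none of them as fact:

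- **That allocation happens the instant the survey is finished.** The word describing assignment as automatic concerns how the sequence works while concealing allocation. No immediacy is stated.
- **That fraudulent accounts use up the 500 places.** Replacement is simply not addressed.
- **That screening differs by arm.** The zip-county, staff-contact and profile checks are worded for everyone, controls included. Only suspicion based on behaviour can be arm-specific. The Discussion's group monitoring is aimed at problem content and is not linked to authenticity checks.

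It is also fair that the fraud and detection rates are assumptions, and that the primary outcome needs a mailed kit and photographs, which hinders false entrants in both arms. With three measures, power stays above 80% at 10% removal. Finally, removal that used only pre-allocation information, judged blind to arm, would cost sample but would not bias the comparison.

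**Conclusion.** The concern holds in a limited form. As written, the plan permits fraudulent or ineligible accounts to be allocated and removed afterwards. It leaves open whether they count toward the 500, and it allows removal to draw on group behaviour that exists only in the intervention arm.

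The likely cost is some power. At an assumed 10% unreplaced removal, power is about 76% on the two-measure basis or about 81% with three measures. Bias is possible, mainly in the self-reported comparison. Under the assumed 90% and 50% detection rates, a 5.1-point difference would show as 4.1 to 0.9 points for fraud shares of 5% to 20%. In the same scenario the verified primary difference shifts by at most about 0.2 points; in the more extreme case of step 5, by about 0.9. All these sizes rest on rates the document does not supply.

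This is an avoidable weakness with a cheap remedy. It is not a demonstrated bias in the primary result.

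**What to change.** In Study procedure:

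1. State that allocation is released only after the planned checks are closed (zip-county agreement, profile review, staff contact where answers conflict), using the same checklist for every applicant.
2. State that only verified, allocated participants count toward the 500. If 10% of baseline completers failed verification, 500 / 0.90 = 556 would be needed; at 20%, 500 / 0.80 = 625.

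In Data analysis, for fraud found after allocation:

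3. Keep the participant in the main analysis unless exclusion rests only on information recorded before allocation and is judged by someone blind to arm.
4. Report exclusions by arm with reasons, and show a sensitivity analysis that leaves out all flagged cases.

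The cost is a hold step in the enrolment software and a short delay before allocation. The checks are already planned, and the delay fits the wait of about two weeks, counted from a group's first enrolment, before that group starts. If staff already verify before allocating, one sentence saying so settles the first item.

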### Development of the intervention

This intervention was adapted from the TSP described above. The TSP is a smoking cessation intervention for young adults that was delivered through private Facebook groups and utilized the US Clinical Practice Guidelines for smoking cessation [43] and the TTM of behavior change [44, 45], with counseling messages tailored to participants’ readiness to quit delivered in 90 Facebook posts over 90 days along with weekly live counseling chat sessions with a trained smoking cessation counselor. The first adaptation of the TSP by our team was to tailor intervention content for sexual and gender minority (SGM) young adult smokers and had preliminary evidence for the effectiveness: an SGM-tailored Facebook smoking cessation intervention increased reported abstinence from smoking, compared to a non-tailored intervention [46]. This study followed the similar adaptation approach as the SGM project to tailor the intervention content for adolescents and young adults who vape: revising the intervention based on extensive iterative formative work. We have an established partnership with HopeLab (a social innovation lab focusing on designing science-based technologies to improve the health of teens and young adults) and with Rescue (a marketing agency providing behavior change marketing services) for intervention adaptation. Before our study, Rescue conducted 18 focus groups and 66 interviews with 269 adolescents to develop adolescent vaping messaging for cessation and interviewed 380 adolescents with vaping experience. Our partners worked intensively in 2021 to further develop the Instagram intervention for adolescents who vape, including co-creation sessions working with 9 adolescents. Surface-level tailoring [47] was accomplished using pictures of adolescents who vape, as well as symbols and terms that were meaningful to the group. Deep-level tailoring [47] involved discussion of adolescent issues relevant to vaping. Examples included increasing awareness of predatory marketing targeting young people, awareness and experiences of addiction, and education about the gateway effect of vaping on smoking initiation. Two design sprints and development of the websites and infrastructure were completed prior to launching a test version of the intervention. 90 adolescents who vape participated in the pilot tests to address the feasibility, acceptability, usability, and helpfulness of the test version. Participant surveys included ratings of different elements of the intervention, and interviews addressed their experience participating in different aspects of the intervention, what they liked most and least about the experience, and identified which aspects of the intervention or procedures to retain or change. The partner team met virtually on a weekly basis throughout the development process until January 2022.

#### Intervention group

The vaping cessation intervention will be implemented on Instagram. Participants in the intervention group will be assigned to groups on Instagram, where they will receive up to 3 posts per weekday for 25 days (5 weekdays, no weekends) over 5 weeks. Posts incorporate skills from cognitive behavioral therapy, found effective for long-term smoking cessation [48], as well as the TTM processes of self-liberation (e.g., making a commitment to quit), stimulus control (e.g., removing vaping paraphernalia from the home), and counter conditioning (e.g., engaging in alternative behaviors). Posts also encourage setting a quit date and making a detailed quit plan. Posts include a combination of images, videos, and text to elicit a response from participants. Posts may suggest that participants use their social media or real social networks for support with vaping cessation. However, they are not required to share any information about substance use on social media.

Groups are facilitated by a trained Guide, a certified cessation counselor with over 4 years of experience facilitating smoking cessation groups on Facebook, working with the Principal Investigator and Sub-Investigators. The Guide will send the daily posts in groups. In addition, the study employs a pediatrician on demand if additional expertise or clinical advice is needed. Participants will be educated about signs of nicotine dependence and if they express interest in pharmacotherapy, we will encourage them to access this through their personal healthcare providers.

#### Control group

Participants in the control condition will be directed to kickitca.org, a website offering links to chatline and texting cessation services operated by the California Smokers' Helpline, the free state quitline program that supports smoking, vaping, and smokeless tobacco cessation strategies.

### Baseline measures

Baseline measures will consist of sociodemographic characteristics, nicotine vaping, quitting experience, motivations to quit (such as readiness to quit vaping, confidence in ability to quit, desire to quit, and commitment to abstinence), other tobacco use, marijuana/cannabis use, social media use integration, and symptoms of depression or anxiety.

### Outcome measures

#### Primary outcome

7-day point prevalence abstinence will be assessed immediately, 3 months, and 6 months after the treatment. Participants reporting no nicotine vaping in the past 7 days will be coded as abstinent. At each follow-up assessment, those reporting 7-day abstinence and not using NRT will be mailed a saliva cotinine test kit for biochemical verification. Participants will be provided both written instruction and a video demonstrating how to correctly perform the saliva cotinine test, and take photos of themselves doing the test and a photo of the result, and how to send the photos to our research staff. Participants with a salivary cotinine level < 20 ng/ml will be considered to have achieved biochemically verified nicotine vaping abstinence.

#### Secondary outcomes

We will measure seven secondary outcomes as below:• Vaping reduction by 50% or more between baseline and each follow-up will be calculated at each time point by multiplying the number of vaping days in the past 7 days and the number of puffs or hits they took on an average day. • Vaping quit attempt will be measured by questions asking the presence and the number of quit attempts lasting at least 1 day since the last assessment. • Readiness to quit vaping will be assessed using the Stages of Change Questionnaire [42] to classify participants as in Contemplation or Preparation phases [45]. Outcome will be measured as proportion change in Stage at assessments conducted immediately, 3 months, and 6 months after the treatment. • Confidence in ability to quit will be measured by asking how confident the participants are about avoiding vaping nicotine in the next 6 months. • Desire to quit will be measured by asking how much the participants want to quit vaping. • Commitment to abstinence will be assessed with the Thoughts About Abstinence Form [49], categorizing their goal as no goal, intermediary goal (e.g., reduced vaping), or total abstinence. Outcome will be measured as proportion endorsing a goal of abstinence at each time point. • Use of evidence-based cessation strategies will be measured by asking the supports participants used when they tried to quit in the past (30 days/3 months). 

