
## Objectives

This study will evaluate the efficacy of the Instagram-based vaping cessation intervention among adolescents and young adults in an RCT. The primary aim is to test the efficacy of the intervention to achieve biochemically verified nicotine vaping abstinence when the treatment ends and sustain it for 6 months after the treatment. The secondary aim is to test the effectiveness of the intervention in terms of decreasing vaping frequency, and increasing quit attempts, readiness to quit, confidence in ability to quit, desire to quit, commitment to abstinence, and use of evidence-based cessation strategies assessed immediately, 3 months, and 6 months after the treatment.

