### Data collection and management

The three follow-up assessments conducted immediately, 3 months, and 6 months after the treatment will be administered online using Qualtrics through UCSF MyAccess, which includes Secure Sockets Layer encryption, and adheres to HIPAA standards, allowing encrypted transmission of all survey data. Research staff will send emails, text messages, and messages in Instagram with the survey links to notify participants of assessments. At most three emails will be sent to remind participants of the assessments. Those who don't respond after the three contact attempts are counted as dropout at each time point. Those who don't respond in the previous assessments will still be contacted for later assessments. For instance, a participant who did not do the assessment at 3 months post-treatment will still be notified of the assessment at 6 months post-treatment up to three times. Survey data will be securely transferred to password-protected Excel or SPSS files that will be securely stored online using the UCSF Research Analysis Environment, a secure, HIPAA-compliant desktop environment. Files with identifying information will be stored separately from files with other forms of data. Data will only be accessed by the PI and a research assistant until it is de-identified. Study investigators have completed required UCSF training and certification in the conduct of research with human subjects. All collected data will be analyzed and reported in aggregate form for publications. All survey data collection and storage procedures are consistent with current HIPAA guidelines.

In order to ensure and maintain the scientific integrity of this human subject research project, and to protect the safety of its research participants, we will assemble a Data Safety Monitoring Board (DSMB). The DSMB will meet every six months via video conferencing to review the study protocol and procedures. The DSMB will have the responsibility of assuring that participants are not being exposed to unnecessary or unreasonable risks as a result of the pursuit of the study’s scientific objectives.

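### Readiness has no stage for people who have quit or lost interest, and quit attempts and strategy use score continuing abstainers at 3 and 6 months like people who never tried

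*Protocol article*

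**What the plan says.** The Secondary outcomes section of the Protocol article defines seven outcomes. Three matter here.

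- **Readiness to quit.** The questionnaire is used "to classify participants as in Contemplation or Preparation phases". The endpoint follows: "Outcome will be measured as proportion change in Stage at assessments conducted immediately, 3 months, and 6 months after the treatment".
- **Quit attempts.** Participants are asked about "the presence and the number of quit attempts lasting at least 1 day since the last assessment".
- **Evidence-based strategies.** Participants are asked about "the supports participants used when they tried to quit in the past", with a look-back of 30 days or 3 months.

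The Objectives section treats a rise in each as benefit; the secondary aim includes "increasing quit attempts, readiness to quit, confidence in ability to quit, desire to quit, commitment to abstinence, and use of evidence-based cessation strategies". The Secondary analysis section models all seven outcomes over time with mixed logistic and multinomial models and gives no rule for participants who are abstinent. Inclusion criterion 6 admits only people who are considering, or interested in, quitting within six months.

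**The concern.** The two readiness stages fit the people who enter the trial. They do not fit everyone at follow-up. The trial aims to move people out of both stages by getting them to quit, and some will move the other way and lose interest. Neither group has a category, so a change-in-stage endpoint can register only movement between the two middle positions.

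Quit attempts and strategy use have a different problem. Both look back over a limited window. A participant who quit during treatment and has not vaped since can truthfully report no new attempt, and no supports used while trying, at 3 and again at 6 months. That answer is the same as the answer of someone who never tried. On the count of attempts, several failed attempts outrank one that lasted.

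Because more of these outcomes is read as better, the scoring penalises whichever arm has more lasting quitters. A report could then say that the intervention produced abstinence without raising readiness or attempts, when part of that pattern came from the coding.

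**Working it through.** **The plan's own figure.** The article gives no rates for these secondary outcomes. Its only related figure is the sample size for the primary outcome (Sample size estimation: 3.2% against 8.3%, alpha 0.05, power 0.80, rho 0.43). A two-sided pooled test at one time point needs 326 per arm. Multiplying by (1 + 0.43)/2 = 0.715 gives 233.1, which rounds up to the stated 234. I use 234 per arm below. This reproduction does not decide the point.

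**Readiness.** No formula is needed. Stages named: Contemplation, Preparation. Possible states at follow-up: not considering quitting, Contemplation, Preparation, already quit. Two of the four have no place. At the planning rates, 234 × 0.083 = 19.4 intervention and 234 × 0.032 = 7.5 control participants would be abstinent, and so without a stage, at a follow-up. The number who lose interest is unknown.

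**Quit attempts, by assessment.**
- End of treatment: the previous assessment is baseline. Anyone who quit during treatment made an attempt in the window and is counted.
- 3 and 6 months: anyone who quit or re-quit within the interval is counted. Anyone abstinent through the whole interval has no new attempt and scores zero.

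**Size of the shift.** Let a0 and a1 be the proportions continuously abstinent across the interval (control, intervention), and q0 and q1 the attempt rates among everyone else.

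- As written: D_w = (1 − a1)q1 − (1 − a0)q0
- Continuous abstainers credited: D_c = [a1 + (1 − a1)q1] − [a0 + (1 − a0)q0]
- Hence D_c − D_w = a1 − a0, whatever q0 and q1 are.

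**Illustration.** Assumptions, not in the documents: a0 = 3.2% and a1 = 8.3% (the planning point-prevalence rates standing in for sustained abstinence); q0 from 30% to 70%; one time point; two-sided 0.05.

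| q0 | q1 − q0 | D_w, points | D_c, points | Power as written | Power credited |
|---|---|---|---|---|---|
| 30% | 0 | −1.53 | +3.57 | – | – |
| 50% | 0 | −2.55 | +2.55 | – | – |
| 70% | 0 | −3.57 | +1.53 | – | – |
| 30% | 10 | +7.64 | +12.74 | 0.42 | 0.81 |
| 50% | 10 | +6.62 | +11.72 | 0.30 | 0.73 |
| 70% | 10 | +5.60 | +10.70 | 0.26 | 0.78 |

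First row in full: 0.917 × 0.30 − 0.968 × 0.30 = 0.2751 − 0.2904 = −0.0153. Credited: (0.083 + 0.2751) − (0.032 + 0.2904) = +0.0357. The gap in every row is 8.3 − 3.2 = 5.1 points.

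**Range.** Seven-day abstinence does not mean abstinence through the interval. If the same share f of point-prevalence abstainers in each arm was abstinent throughout, the shift is f × 5.1 points: 2.55 at f = 0.5, and 5.1 at most. A different true gap in sustained abstinence would move the outcome by that gap; an assumed 10-point gap would move it by 10.

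**Strategy use.** The mechanism is the same, but only sustained quitters who used a support in their successful attempt are lost. The quit-attempt shift therefore equals the strategy-use shift only if all of them used one, or the same number of points did not in each arm.

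**The case against.** The strongest defence is of readiness. The two stages may describe entrants only: criterion 6 confines entry to people considering quitting, readiness is also a baseline measure, and multinomial models can carry more than two stages. The full questionnaire or analysis plan may place abstainers. That is possible, but the article names the two stages in the outcome definition itself and applies the change in stage to all three follow-ups. For commitment to abstinence the same section lists the whole range, from no goal to total abstinence.

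A second defence is that attempts per interval are a coherent repeated measure, and that crediting abstainers builds part of the primary outcome into a secondary one. This stands as a cost of the fix. It does not make a zero for a lasting quitter interpretable when more attempts are read as benefit. Some continuing abstainers may also report their ongoing quit as an attempt, but the scoring would then depend on how each respondent reads the question.

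Stronger readings are tempting and should be resisted:

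- A reader might infer that all three outcomes are defined only for people still vaping. Attempts and supports are not restricted in that way, and quitting within the window counts.
- A reader might take 8.3% and 3.2% as the proportions misclassified on attempts and strategy use at every follow-up. They are point-prevalence rates, and the attempt item works at end of treatment.
- A reader might infer that abstainers are dropped and the models compare unlike subsets. Nothing in the analysis sections says so.
- A reader might infer unequal windows, since people who miss an assessment "will still be contacted for later assessments". The article does not say how the attempt question is worded for them, and strategy use has a stated look-back.

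**Conclusion.** The concern holds in a limited form. For readiness, the definition as written has no stage for the best or the worst movement at any follow-up; how far this biases the comparison depends on how those participants are coded, which the article does not say. For quit attempts and strategy use, the defect is confined to people abstinent across a whole interval, at 3 or 6 months.

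The quit-attempt bias equals the between-arm difference in sustained abstinence and runs against the intervention if it works. The documents give no sustained rate. With the planning rates as a stand-in, and the same share of abstainers sustained in each arm, it is at most about 5 points. Under the assumed attempt rates, that ceiling would cut single-time-point power for a true 10-point effect among the rest from 0.73–0.81 to 0.26–0.42.

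It would go too far to say that the trial's benefit is hidden. Quitters are fully credited in the primary abstinence outcome and in the outcome of reducing vaping by half or more. The damage is to the interpretation of three of the seven secondary outcomes.

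**What to change.** 1. **Readiness.** At follow-up, use the full set of stages, adding not considering quitting and already quit, with already quit as the most advanced. Analyse forward movement in all randomised participants.
2. **Quit attempts.** At 3 and 6 months, score continuous abstinence since the last assessment as a successful attempt. Alternatively, keep the interval item and add any attempt of at least one day since randomisation as a companion measure. The cumulative measure cannot fall over time, so it answers a different question and should not simply replace the interval item.
3. **Strategy use.** Report it so that sustained quitters are credited with the supports they used in their successful attempt, and state which look-back and denominator apply at each follow-up.

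The cost is minor survey wording and coding rules, with no extra assessments. The drawback is that the quit-attempt outcome then overlaps slightly with abstinence, which the report should state.
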